### C. Subject Recruitment Plans and Consent Process

There are two routes for volunteer screening:

#### i. For subjects who participated in the Stage 2 trial.

On Visit 10, subjects are invited to participate to this follow-up research and written informed consent is solicited: Explain the study and Informed consent document (ICD) to the subject; ensure that the subject signed and received a copy of the ICD. The number of subjects who gave informed consent and their place of residences will be noted and takes an important consideration for the second route of volunteer screening-- the screening for control cohorts.

#### ii. For volunteers who will serve as additional control cohorts.

After obtaining the number of subjects willing to participate in the one-year follow-up at Visit10, during the 40-day passive surveillance, healthy volunteers will be recruited to make up the control arm:

Explain the study and ICD to the volunteer; ensure that the volunteer signed and received a copy of the ICD

Elicit a complete medical history; administer a complete physical examination; obtain blood for hematology, biochemistry, malaria smear; obtain urine for urine dipstick testing, as well as urine  $\beta$ -hCG testing for females. *To be an appropriate/adequate control group, the volunteers to be enrolled should essentially be representative of the population from subjects that gave consent to participate in the longitudinal study.*

These individuals will receive oral and written explanation of the study, after which consent will be obtained from those willing to participate. All screening tests, medical history and examinations will be performed only after consent is obtained. Individual consent process will be conducted in separate consultation rooms to ensure confidentiality. Any clinically relevant finding that is discovered upon screening will either be treated appropriately or referred for more comprehensive diagnosis and treatment. Study clinicians will generally handle acute, simple conditions such as malaria (or other infections) but more complicated or chronic renal or heart disease will be referred to appropriate sources of medical care. Volunteers will provide a medical history, with special attention to any history of recurrent infections to suggest immune suppression. They will also undergo physical examination and laboratory screening tests. A participant who meets any of the exclusion criteria will be managed initially by study clinicians and referred to the local health center for evaluation as necessary.

### D. Detailed description of study visits:

**Study practice:** Medical interview, consultation and serum sampling once every four weeks for 11 months

#### At each monthly visit:

- 1 Consultation/examination of injection site (for administered subjects) if there are unresolved AEs
- 2 Consultation interview for recent illness, malaria symptoms; includes capturing malaria incidences between visits
- 3 Vital signs (temperature, blood pressure, pulse rate)
- 4 A few drops of blood sampling (by finger prick) for malaria smear, filter paper blots, and ELISA assay.
5. Blood draw (4 mls) of venous blood for serum sampling

Subjects will be assigned to fall into different consultation days. Clinic visits will be in groups. Care should be exercised whenever possible that the BK-SE36 administered cohort group can be matched to a control cohort group in the same locality for equal "bias" in malaria incidence rates.

During this follow-up period, adverse events will not be reported but malaria episodes will be documented and blood samples collected for immunological testing. Daily body temperature monitoring and recording by participants or parents /guardians will be carried out by the participants themselves at home throughout the study period. Training of participants and /or parents/guardians in the use of thermometers, reading and recording of body temperatures will be conducted during the start of the study

At the final visit:

Blood sampling (20-ml venous blood) for ADCl and ELISA assays

Passive follow-up for malaria will consist of visits to LMC trial site whenever the subject is sick. During each visit, the subject will be evaluated and a malaria smear will be done whenever malaria is suspected. During the course of evaluation for malaria, other illnesses maybe uncovered in the study subjects, such as upper respiratory infections, and other bacterial or viral infections. The pharmacy can provide subjects with common over-the-counter analgesics such as paracetamol as well as antibiotics for the treatment of minor ailments and infections. If further evaluation or treatment is necessary, the subject will be referred to the hospital arm in LMC.

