**Other trial activity/Blood sampling:**

A few drops of blood will be taken from all subjects for the following:

1. Parasitemia determination: for confirmation of parasitemia by standard microscopy
2. Filter paper blood spots: A thick blood smear is made. *P. falciparum* DNA will be amplified for molecular genotyping of SERA gene polymorphism)
3. Serum preparations for *ELISA measurements on antibody titres against SE36 as well as several malaria antigens*

Blood drawn at the final visit shall be used for the following assays as well:

4. ELISA Assays with synthetic peptides covering SE36 molecule (epitope recognition)
5. Growth inhibition studies (ADCl)
6. Other biological studies, such as HLA haplotype typing

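### At unscheduled sick visits the malaria smear depends on undefined suspicion by staff not stated to be masked, who can recognise 48 of the 66 controls, so between-visit malaria incidence may be ascertained unequally

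*Protocol*

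**What the plan says.** **Unscheduled visits.** Section D sets up detection between appointments as follows: "Passive follow-up for malaria will consist of visits to LMC trial site whenever the subject is sick". At such a visit "a malaria smear will be done whenever malaria is suspected". No fever threshold, symptom list or other criterion defines suspicion. The same paragraph foresees that some sick subjects will turn out to have other infections and be treated for those.

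**Scheduled visits.** Section D also provides for "Medical interview, consultation and serum sampling once every four weeks for 11 months". Item 4 of the monthly list is "A few drops of blood sampling (by finger prick) for malaria smear, filter paper blots, and ELISA assay", with no condition of suspicion. The blood-sampling list repeats that "A few drops of blood will be taken from all subjects for the following", parasitaemia by microscopy being the first use. Item 2 is an interview that also picks up malaria since the last visit.

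**Home temperature.** "Daily body temperature monitoring and recording by participants or parents /guardians will be carried out" throughout the study. No threshold, visit or smear is attached to the readings.

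**Who can be recognised.** Synopsis item 7 makes up the control group from 9 + 9 placebo recipients and 48 volunteers who receive nothing. Section C.ii recruits and screens those 48 separately, during the 40-day surveillance period. Item 1 of the monthly list is "Consultation/examination of injection site (for administered subjects) if there are unresolved AEs". On scheduling, section D says "Care should be exercised whenever possible that the BK-SE36 administered cohort group can be matched to a control cohort group", within the same locality.

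**Use of the data.** A4.1 lists malaria incidence and treatment incidence density among four primary endpoints. A3.2 wants baseline data on vaccine efficacy, and section E item 5 compares counts of mild and severe malaria between BK-SE36 and control. Section H provides subject codes, but no section masks clinicians or microscopists.

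**The concern.** Whether a sick subject gets a smear between scheduled visits rests on a judgement that the protocol does not define. Section A2 itself notes that malaria can be mistaken for other illnesses, so there is real room for discretion. The people exercising it can know that a subject is one of the uninjected controls, and nothing is said about keeping group from them or from the person reading the slide.

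If malaria is suspected more or less readily in uninjected subjects, the counts in the two groups differ for a reason unrelated to the vaccine. A smear that was never taken cannot be recovered in the analysis, so this has to be settled in the data-collection section and cannot wait for a SAP. An objective measure, daily temperature, is already collected from every subject but does not standardise the trigger.

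**Working it through.** **Group sizes (Synopsis item 7).** 33 + 33 + 9 + 9 + 48 = 132, which reproduces the stated total. Vaccinees number 33 + 33 = 66 and controls 9 + 9 + 48 = 66. Untreated controls are 48/66 = 72.7% of the control group. The protocol states no event rate, effect size or power, so there is no stated precision to check.

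**What the scheduled smears cover.** Eleven months at four-week spacing is 11 × 365.25/12/28 = 11.96, or about 12 visits. Each smear samples one day in 28. Section A1 says school-aged children are at highest risk of asymptomatic parasitaemia, so a positive scheduled smear is not in itself a clinical episode. Scheduled smears therefore give a parasitaemia measure free of suspicion, but they cannot replace detection of illness between visits.

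**Illustration with no true vaccine effect.** All probabilities here are assumed; none comes from the protocol. Let s_i be the chance that an episode in an injected subject (vaccine or placebo) is smeared at a sick visit, s_u the same chance in an untreated subject, and f the share of episodes found only through that route. The rest are found independently of suspicion.

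- Ascertainment in injected subjects: a_i = f·s_i + (1 − f)
- Ascertainment in untreated subjects: a_u = f·s_u + (1 − f)
- Control group: c = (18·a_i + 48·a_u)/66
- Observed rate ratio: a_i/c

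The 18 placebo subjects are given the vaccinees' value because the protocol supports recognition of uninjected subjects only.

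| f | s_i | s_u | a_i | c | Rate ratio | Apparent efficacy |
|---|---|---|---|---|---|---|
| 1.0 | 0.8 | 1.0 | 0.80 | (14.4 + 48)/66 = 0.945 | 0.846 | 15.4% |
| 0.5 | 0.8 | 1.0 | 0.90 | (16.2 + 48)/66 = 0.973 | 0.925 | 7.5% |
| 1.0 | 0.9 | 1.0 | 0.90 | (16.2 + 48)/66 = 0.973 | 0.925 | 7.5% |
| 0.5 | 0.9 | 1.0 | 0.95 | (17.1 + 48)/66 = 0.986 | 0.963 | 3.7% |
| 1.0 | 1.0 | 0.8 | 1.00 | (18 + 38.4)/66 = 0.855 | 1.170 | −17.0% |
| any | equal | equal | – | = a_i | 1.000 | 0% |

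The fifth row reverses the assumption and gives apparent harm, so the direction is as uncertain as the size.

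**Effect on a test.** Person-time is 66 × 11/12 = 60.5 person-years per group. Take Poisson counts and a two-sided 5% Wald test on the log rate ratio. With the first row's values and one episode per person-year (assumed), expected counts are 60.5 × 0.80 = 48.4 and 60.5 × 0.945 = 57.2. Then z = 0.167/√(1/48.4 + 1/57.2) = 0.86, and the false-positive rate is about 14%. At 0.5 and 2 episodes per person-year it is about 9% and 23%. With f = 0.5 the range is about 6% to 9%. With equal ascertainment it stays at 5%.

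**The case against.** The strongest reply is that this is an observational follow-up seeking baseline data, in which passive detection on suspicion is a legitimate choice. Every subject is smeared about 12 times whatever anyone suspects. The monthly interview and the questionnaire in section N also record malaria since the last visit, treatment elsewhere and self-medication. This stands as mitigation. It does not standardise the between-visit smear, and the interview relies on recall, with interviewers also not stated to be masked.

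A reader might also infer three stronger points that the document does not support.

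- **That a smear is taken only when a clinician suspects malaria, and that this smear decides who is a case.** The four-weekly smears contradict the first half. The second half is inference, because no case definition is given and section A2 acknowledges the need for one.
- **That staff can tell vaccine from placebo.** The matching sentence names no actor and applies only where possible. Injection-site examination covers all administered subjects, and only those with unresolved adverse events, so it does not separate BK-SE36 from saline. Whether Stage 2 allocation is known during follow-up is not stated.
- **That all primary endpoints are compromised.** Anti-SE36 titre and parasitaemia from scheduled smears do not pass through this route. Treatment incidence density counts treatments, including those recorded from outside the site, so its dependence on the smear is possible but not shown. Section E item 5 averages parasitaemia over all samples, so that measure is touched only if samples taken on suspicion are pooled in.

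**Conclusion.** The point holds in limited form. Between-visit malaria incidence, and possibly treatment incidence density, is open to differential ascertainment. The smear trigger is undefined, no masking of clinicians or readers is stated, and 73% of the control group is recognisably uninjected. The scheduled smears and monthly interview lessen this but do not remove it.

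The size and direction cannot be determined from the protocol. Spurious efficacy of about 15%, or 7.5% if half the episodes are found independently, is an illustration. It rests on assumed smear probabilities of 0.8 and 1.0, no true effect, and staff who recognise only the untreated subjects.

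The change is worth making before data collection because it is cheap and analysis cannot replace smears that were never taken.

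**What to change.** In section D, for endpoint ascertainment:

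1. Take a study smear at every unscheduled sick visit that meets one pre-specified objective criterion, based on the temperature at the visit or in the home log already kept, and applied identically to all groups. The investigators should set the value. The 37.5 °C in exclusion criterion <1> was written for the time of vaccine administration and should not be carried over without justification.
2. Count smear-confirmed episodes in the primary incidence comparison only if they meet that criterion. Smears taken on clinician suspicion alone remain allowed and are analysed separately.
3. Label slides with the subject code only, so that the existing microscopists read without knowing group.
4. Add two sensitivity analyses, one limited to scheduled smears and one to vaccine versus placebo. In the illustration the second gives 0.8/0.8 = 1.00, provided allocation is not known. It is imprecise: placebo person-time is 18 × 11/12 = 16.5 years, so at an assumed one episode per person-year the 95% limits around a ratio of 1 are exp(±1.96 × √(1/60.5 + 1/16.5)), or 0.58 to 1.72.

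This sets no rule for when families attend or for treatment.

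The cost is wording in section D and some extra smears. Two limits remain: attendance is still initiated by the subject, and home readings are recorded by families who know whether the child was injected.

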**Other trial activity/Blood sampling:**

A few drops of blood will be taken from all subjects for the following:

1. Parasitemia determination: for confirmation of parasitemia by standard microscopy
2. Filter paper blood spots: A thick blood smear is made. *P. falciparum* DNA will be amplified for molecular genotyping of SERA gene polymorphism)
3. Serum preparations for *ELISA measurements on antibody titres against SE36 as well as several malaria antigens*

Blood drawn at the final visit shall be used for the following assays as well:

4. ELISA Assays with synthetic peptides covering SE36 molecule (epitope recognition)
5. Growth inhibition studies (ADCl)
6. Other biological studies, such as HLA haplotype typing

**E. Statistical considerations**

The purpose of this study is to estimate malaria episodes, patterns of immune responses as well as compare these rates and patterns in different doses/interventions of the study based on the Phase 1b, stage2 protocol. Listings will show all observed data. Should there be a need for early termination of the study, available data will be analyzed and interpreted in light of early termination.

To assess and compare the duration of specific antibody response to SE-36 over a 11 month period:

1. A test will be performed to check for any significant differences in the antibody concentrations of the two dose groups.

2. Immunogenicity responses by vaccine and dose group will be described over time. Individual responses can also be described over time and stratified by dose cohort.
3. For antibody concentrations measured, a longitudinal model will be built to describe the antibody response over time. The model will also explore if there are any differences between the two doses used for Stage2.
4. Waning will be assessed by comparing levels of antibody with time, as well as malaria infection.
5. Average parasitemia in all samples collected during the whole period will be compared between the vaccine and placebo group (including number of incidences of mild and severe malaria in BK-SE36 vs. control groups). Kaplan-Myer plots will be used to compare the immunological protection between blood parasitemia levels and administration of BK-SE36

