### 2. Objectives:

- a) To compare long term immunogenicity of BK-SE36 malaria vaccine and antibody response to natural malaria infections in children who participated in the BK-SE36 malaria vaccine trial in Uganda.
- b) To compare malaria incidence rates and severity between volunteers who received BK-SE36 vaccine (at half or full dose) and those who received placebo or no administration (control group).

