### **Study hypothesis.**

For continued development of BK-SE36, we propose to study the long term immunogenicity of BK-SE36 malaria vaccine and antibody response to natural malaria infections and to compare malaria

incidence rates and severity between volunteers who received BK-SE36 vaccine (at half or full dose) and those who received placebo or no administration (control group). We hypothesize that:

- (1) BK-SE36 cohorts will show higher antibody titres after malaria natural infection than right after administration of BK-SE36. This phenomenon is known as a natural booster effect and an important element to be considered for vaccine strategy;
- (2) BK-SE36 cohorts will show higher antibody titres against the protective epitopes in SE36 molecule; and
- (3) Malaria incidence, severity and treatment incidence density will be lower in participants who received the BK-SE36 vaccine compared to the controls who received physiological saline or no intervention

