### **A3. Objectives**

A3.1. To analyze the antibody productions quantitatively and qualitatively in volunteers who experiences natural malaria infection, and those who were not able to experience malaria infection in both vaccinated and non-vaccinated groups for obtaining a baseline data of biological effects.

A3.2. To compare malaria infection rates and severity in both of vaccinated and non-vaccinated groups for obtaining a baseline data of vaccine efficacy.

A3.3. To undertake SERA5 polymorphism study of *P. falciparum* in severe malaria incidences

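### Section E names no vaccine-versus-control antibody comparison, and hypothesis (1) judges natural boosting within vaccinees alone

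*Protocol*

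**What the plan says.** **Objectives.** Synopsis objective (a) reads "To compare long term immunogenicity of BK-SE36 malaria vaccine and antibody response to natural malaria infections in children who participated". Section A3.1 is more specific. It asks for quantitative and qualitative antibody analysis in volunteers who have a natural infection and in "those who were not able to experience malaria infection in both vaccinated and non-vaccinated groups". Section A4.1 lists change in anti-SE36 titre first among the primary endpoints.

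**Analysis (Section E).**
- Item 1: "A test will be performed to check for any significant differences in the antibody concentrations of the two dose groups".
- Item 2: "Immunogenicity responses by vaccine and dose group will be described over time".
- Item 3: a longitudinal model of antibody over time, for which "The model will also explore if there are any differences between the two doses used for Stage2".
- Item 4: "Waning will be assessed by comparing levels of antibody with time, as well as malaria infection".
- Item 5 sets vaccine against placebo or control, but for parasitemia and malaria episodes.

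**Boosting criterion.** Hypothesis (1), under Study hypothesis in Section A1, is that "BK-SE36 cohorts will show higher antibody titres after malaria natural infection than right after administration of BK-SE36". The protocol calls this a natural booster effect. The epitope-shift comparison in Section A2.3 is likewise made among vaccinated sera, with and without infection.

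**Controls.** The Synopsis plans 66 vaccinees and 66 controls: 18 placebo recipients from Stage 2 and 48 added volunteers who receive nothing. Section B2.3 says that the added subjects are needed for comparison with the vaccinated cohorts. Section D takes blood for the SE36 ELISA from every subject.

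**The concern.** A3.1 defines four cells: infected or not, by vaccinated or not. The only antibody contrast that Section E names stays on the vaccinated side of that table and compares half dose with full dose. The antibody data from the controls have no named comparison.

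Hypothesis (1) has the same gap. A titre that rises after infection in a vaccinated child could mean that the vaccine primed the response. It could also be the response an unvaccinated child would have made. Section A1 says that natural responses to SE36 are widespread and age-dependent in the earlier immuno-epidemiological work, so the second explanation is live. Without a control contrast the study could credit the vaccine with ordinary acquired immunity, and Section A2.1 draws its inference about protection from such boosting.

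Item 4 has a related weakness. In exposed children, titre over time mixes decay with renewed stimulation by infection, and no control comparison is named to help separate them.

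**Working it through.** **1. Sample size.** 33 + 33 + 9 + 9 + 48 = 132. Vaccinated: 33 + 33 = 66. Control: 9 + 9 + 48 = 66. The stated total is reproduced. The protocol gives no alpha, power, effect size, titre SD or infection rate, so those used below are assumptions.

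**2. What is asked against what is named.**

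| Question | Source | Comparison named for it in Section E |
|---|---|---|
| Antibody by infection status, vaccinated and non-vaccinated | A3.1 | None between vaccinated and control |
| Half against full dose | Section E | Item 1 (test), item 3 (model) |
| Antibody by vaccine group | Section E | Item 2, descriptive |
| Waning | A2.2 | Item 4, against time and infection, no control contrast |
| Parasitemia and episodes, vaccine against control | A3.2 | Item 5 |

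**3. What a before-after test responds to.** Suppose infection produces the same net rise in both groups, so the vaccine has no effect on the response. Changes are simulated as normal with SD 1, tested two-sided at 0.05, with 5,000 data sets per setting. The table gives how often a before-after test in infected vaccinees declares a rise.

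| Infected vaccinees (of 66) | Rise 0.25 SD | Rise 0.5 SD | Rise 0.75 SD |
|---|---|---|---|
| 20 (30%) | 18% | 57% | 89% |
| 33 (50%) | 28% | 81% | 99% |
| 46 (70%) | 38% | 92% | 100% |

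The vaccinated-versus-control test of the rise stays at about 5% throughout. The before-after test detects a rise and cannot say where it came from.

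**4. Waning changes the frequency.** Hypothesis (1) takes the titre just after vaccination as reference, so any waning before infection is subtracted. With rise r from the pre-infection level, waning w, SD of change s and n infected vaccinees, the chance of meeting the criterion is Φ((r − w)/(s/√n) − 1.96). Assume r = 0.25 log10, s = 0.5 log10 and n = 40, so s/√n = 0.079.
- w = 0.1: Φ(0.15/0.079 − 1.96) ≈ 47%
- w = 0.2: Φ(0.05/0.079 − 1.96) ≈ 9%
- w = 0.25 or more: at most 2.5%

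The formula does not depend on why the titre rose. With enough waning, a rise that the vaccine did prime would fail the criterion just as often. The criterion can mislead in both directions.

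**5. What the control contrast can deliver.** Detectable difference in SD units at 80% power, two-sided 0.05, is (1.96 + 0.84) × √(1/n₁ + 1/n₂).
- Dose against dose, 33 v 33: 0.69 SD; power at 0.5 SD is 53%.
- Vaccine against control, 66 v 66: 0.49 SD; power at 0.5 SD is 82%.
- Infected vaccinees against infected controls: 0.89, 0.69 and 0.58 SD with 30%, 50% and 70% infected in each group.
- Four-cell vaccine-by-infection interaction: 0.98 to 1.06 SD over the same range.

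These ignore dropout and any gain from repeated measures.

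**The case against.** **The model is not closed to a control contrast.** Section E opens by saying that immune response patterns will be compared across doses and interventions. Item 3 says the model will *also* look at dose, so that contrast is an addition, and nothing restricts the model to vaccinees. Model terms are commonly left to a statistical analysis plan. All of this stands. A reader might infer that the first objective is never tested, and the text does not support that. It supports only that no vaccine-versus-control antibody comparison is named while dose against dose is. The opening sentence attaches no analysis to its intent.

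**The before-after criterion is in the hypothesis.** No item in Section E prescribes it, so the hypothesis itself needs rewording too.

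**The frequency of error is unknown.** A reader might set waning to zero in step 4 and conclude that an unprimed rise would be taken for boosting about 88% of the time. The protocol gives neither the rise nor the waning, and modest waning removes most of that figure.

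**Origin of change.** A reader might also infer that change is measured from study start, with vaccinees near their peak. No passage fixes the origin, and follow-up starts only after the 40-day surveillance period of Stage 2.

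**Section A1 reports no post-infection rise in unvaccinated people.** It reports widespread natural antibody, with adults split into sero-positive and sero-negative. An ordinary response to infection is therefore a plausible inference, and that is enough to leave the vaccinee-only comparison ambiguous.

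**The controls may serve incidence as much as antibody.** Section B2.3 cites length of follow-up, drop-out and equal opportunity for infection. That is fair, but their sera are assayed for SE36 all the same.

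**Conclusion.** The point holds as a mismatch between A3.1 and Section E. The objective calls for vaccinated and non-vaccinated groups by infection status, and the only named antibody contrast is between doses. It also holds for hypothesis (1), whose within-vaccinee comparison cannot attribute a rise to the vaccine. An unseen analysis plan could add the missing term, but the protocol's own named test and hypothesis would still not match A3.1.

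The reasoning rests on the text and on natural SE36 antibody being common. It needs no particular effect size. The error rate cannot be stated: the figures in step 4 run from at most 2.5% to about 47% over assumed waning of 0.1 log10 or more, with the rise, SD and number infected also assumed. Nothing is lost irrecoverably, because the plan already collects serum and smears from both groups every four weeks.

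**What to change.** Change Section E items 1, 3 and 4, and hypothesis (1):
- Name as the main antibody analysis a vaccine-versus-control comparison of log titre across the monthly visits, within the longitudinal model, adjusted for age, locality and control source (placebo or added volunteer).
- Add time-varying smear-confirmed infection and a group-by-infection term: the rise from the last pre-infection to the first post-infection serum, vaccinated against control. Report it as an estimate with a confidence interval, not as a powered primary test.
- Assess waning in infection-free intervals, against controls.
- Keep half against full dose as a secondary comparison.
- Reword hypothesis (1) so that any boosting attributed to the vaccine rests on the contrast with controls.

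The cost is wording and analysis time, with no extra sampling. The limits should be written in. The 48 added controls were not randomised. Infection occurs after vaccination, and hypothesis (3) expects the vaccine to reduce malaria incidence, so conditioning on infection may select different children in the two groups. By step 5 the infection-related estimates will be imprecise. They should be read as associational.

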### 3. Outcome:

**1)** antibody response as a result of natural malaria infections; **2)** malaria incidence; **3)** treatment incidence density (treatments per time at risk); **4)** prevalence of malaria parasitemia and parasite density for each group that received BK-SE36 vaccine (at half or full dose) and those who received placebo or no administration (control group); **5)** change in antibody titres/epitope recognition against synthetic short peptides *spanning the whole length of SE36*.

**4. Study site:** Lira Medical Centre (LMC), Lira, Uganda

**5. Study design:** Longitudinal observational study in children who participated in the BK-SE36 malaria vaccine trial in Uganda.

**6. Participants:** BK-SE36 Phase1b Stage2 study subjects (6-20 y old) who give consent for additional 11 months follow-up period, AND additional volunteers for recruitment to achieve an equal number of subjects in the control group (*i.e.* BK-SE36 cohort ( $n=66$ ) = placebo cohort + *additional volunteers* ( $n=66$ )). These additional volunteers that did not participate in Phase 1b Stage2 trial will not be receiving any intervention/administration.

**7. Number of participants:** A total of 132 participants.

(33) subjects = administered with half dose SE36 (50 µg)

(33) subjects= administered with full dose SE36 (100µg)

(9) subjects = administered with half dose of placebo (0.5mL physiological saline)

(9) subjects = administered with full dose of placebo (1.0mL physiological saline)

(48) additional volunteers to be recruited into the control group (no administration)

**8. Expected start date:** End of 40 days surveillance period of Phase 1b, Stage2

**9. Primary completion date:** 11-months after study start

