### **A4. Endpoints: Primary**

A4.1. Change in titers of anti-SE36 antibody, parasitemia rates, malaria incidence, malaria treatment incidence density

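### Section E item 5 averages parasitaemia over all samples without making the subject the unit; if the samples were then treated as independent, the false-positive rate would exceed 5%

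*Protocol*

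**What the plan says.** Section E item 5 sets out the parasitaemia comparison in one sentence: "Average parasitemia in all samples collected during the whole period will be compared between the vaccine and placebo group". A parenthesis adds counts of mild and severe malaria in the vaccine and control groups. Item 5 names no unit of analysis, test, significance level or standard error for the average.

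Item 3 of the same section does provide for repeated measurement, but only for antibody: "For antibody concentrations measured, a longitudinal model will be built to describe the antibody response over time".

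The primary endpoint statement (A4.1) reads "Change in titers of anti-SE36 antibody, parasitemia rates, malaria incidence, malaria treatment incidence density". The synopsis, under Outcome, lists "prevalence of malaria parasitemia and parasite density for each group that received BK-SE36 vaccine".

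Section D sets the schedule: "Medical interview, consultation and serum sampling once every four weeks for 11 months". Each monthly visit includes "A few drops of blood sampling (by finger prick) for malaria smear, filter paper blots, and ELISA assay". Between scheduled visits, subjects attend the site when they are sick, and "a malaria smear will be done whenever malaria is suspected".

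The synopsis plans "A total of 132 participants": 33 + 33 vaccinated, 9 + 9 given placebo, and 48 untreated volunteers who bring the control group to 66.

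**The concern.** The vaccine was given to subjects, but the quantity in item 5 is an average over samples. Smears from one child are likely to resemble each other. The Background (A1) describes chronic parasitaemia in school-aged children, and Section D asks for vaccinated and control groups to be matched by locality because malaria incidence differs between places. If about 12 smears per child are counted as 12 independent observations, the standard error is too small and chance differences are too readily taken as real, in either direction.

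A second effect comes from the words that admit every sample over the whole period. They do not exclude smears taken because a child was ill. In a pooled average, a child with more illness visits contributes more samples, and those samples are more likely to be positive.

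Objective A3.2 is to obtain baseline data on vaccine efficacy, and A2 expects the observations to carry the product into further trials. An interval that is too narrow would mislead that decision.

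**Working it through.** The protocol states no power, significance level, ICC or expected result for this comparison, so there is no figure of its own to reproduce. What follows is conditional on a pooled analysis.

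**Inputs from the protocol**
- Scheduled smears per subject: 11 months at four-weekly visits gives 11 × 30.44 / 28 = 11.96, about 12 (11 if read as one per calendar month).
- Subjects: 33 + 33 = 66 vaccinated; 9 + 9 = 18 placebo; 18 + 48 = 66 controls in all; 66 + 66 = 132.
- Scheduled smears in the vaccine group with full attendance: 66 × 12 = 792.

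**Assumptions**
- Two-sided test at a nominal 5%, no true effect, samples treated as independent.
- Exactly m = 12 smears per subject. Drop-out, which B2.3 anticipates, would lower this.
- ICC varied from 0.02 to 0.50.

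**Formulas**
- Design effect: DE = 1 + (m − 1) × ICC.
- Actual false-positive rate: 2 × [1 − Φ(1.96 / √DE)].
- Width of the pooled interval relative to the correct one: 1 / √DE.

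Example at ICC 0.30: DE = 1 + 11 × 0.30 = 4.3; 1.96 / √4.3 = 0.945; false-positive rate 34.5%. The pooled interval has 1 / √4.3 = 0.48 of its correct width, and 792 smears carry the information of 792 / 4.3 ≈ 184 independent ones.

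| ICC | DE | False-positive rate, formula | Simulated, 66 v 66 | Simulated, 66 v 18 |
|---|---|---|---|---|
| 0.02 | 1.22 | 7.6% | not run | not run |
| 0.05 | 1.55 | 11.5% | 11.2% | 12.0% |
| 0.10 | 2.10 | 17.6% | 16.7% | 16.3% |
| 0.20 | 3.20 | 27.3% | 27.6% | 26.1% |
| 0.30 | 4.30 | 34.5% | 34.5% | 33.7% |
| 0.50 | 6.50 | 44.2% | 44.0% | 44.0% |

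The simulations used a normal outcome and 4,000 runs per setting. With 11 smears instead of 12, the formula gives 7.4% at ICC 0.02 and 42.4% at 0.50, so the exact visit count matters little. The choice between 18 and 66 comparators also matters little.

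**One mean per subject.** In the same simulated data, a t-test on subject means rejected in 4.7% to 5.7% of runs across both comparisons.

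**Illness-triggered smears.** A further simulation used positive or negative smears in 66 v 66 subjects, with mean positivity 0.3, ICC 0.20 and 3,000 runs. Pooling the scheduled smears gave 27.1% false positives. Each subject was then given extra positive smears averaging three times that subject's own positivity, which is an assumed rate, and the figure rose to 32.5%.

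**The case against.** A reader might infer that the protocol makes the blood sample the unit and that false positives will therefore be common. The document does not support either statement. Item 5 says which data enter the average; it does not say how the average is formed or how its uncertainty is computed. It can be read as each subject's average over all of his or her samples, compared between groups. A2 lends that reading some support, since it says parasitaemia will be followed longitudinally in each subject. Item 1 announces a test for the two dose groups, whereas item 5 speaks only of a comparison, so any p-value here is supplied by the reader. A statistical analysis plan, not available here, may specify a clustered analysis, and naming a longitudinal model for antibody does not rule one out for parasitaemia.

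Two smaller points are also fair. A4.1 refers to parasitaemia rates and item 5 to average parasitaemia, and item 5 sits under a lead-in about the duration of antibody response, so its link to the primary endpoint is not spelled out. And the ICC is unknown: at 0.02 the inflation is modest.

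What remains is that the protocol does more than leave detail for later. It states what is averaged, and the literal meaning is a pooled average. An analysis plan faithful to that sentence could adopt the pooled form. If both readings stay open, the unit for a primary parasitaemia comparison could be chosen after the data are seen.

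**Conclusion.** The point holds as a wording fault with a conditional consequence. Item 5 defines the comparison over all samples and does not fix the subject as the unit, although the data are repeated within subjects by design. If it is followed literally with samples treated as independent, the false-positive rate runs from about 8% (ICC 0.02) to 44% (ICC 0.50), subject to the assumptions listed above. On the per-subject reading it stays near 5%. Separately, and whatever standard error is used, a pooled average that admits illness-triggered smears gives more weight to children who are ill more often. The protocol does not show that the pooled analysis will be used, only that its text permits it. The correction should be made because it costs little and this result is meant to inform later trials.

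**What to change.** Reword item 5 so that the subject is the unit and only scheduled four-weekly smears enter the parasitaemia comparison. For example:

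- *Smear positivity* at scheduled visits is compared between groups with a GEE or mixed logistic model, with group and visit as fixed effects, subject as the cluster and robust standard errors.
- *Parasite density* is compared in one of two ways, chosen in advance: on the log scale among positive smears with the same clustering, or as one mean per subject with a stated rule for negative smears. A rule is needed because the logarithm of zero is undefined. The first option describes infected samples only and should be reported as such.
- *Illness-triggered smears* count under malaria incidence and do not enter the average.

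This takes a few sentences in Section E and no new data. There are two costs. Confidence intervals will be wider than those from a pooled analysis. The quantity estimated also changes, because the parasitaemia average no longer includes unscheduled smears, which the present wording admits.
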